### Interventions

#### Moodbuster Lite

Moodbuster Lite is a 4-week therapeutic course aimed at improving mood. It is a light-weight version of the Moodbuster for Depression intervention [26, 27] and consists of a web-based and a mobile component. Compared to Moodbuster for Depression, which also contains a number of cognitive therapy-based modules, the focus of Moodbuster Lite is on behavioral activation [28]. Through activity scheduling, participants learn to turn a “negative spiral,” with few pleasant activities leading to few positive stimuli, a low mood, and little incentive to perform more activities, into a “positive spiral,” with more pleasant activities leading to more positive stimuli, a better mood, and incentive to remain active. A secure web-based platform provides access to online lessons, homework exercises, a mood graph, and a calendar. A smartphone application, designed for both Android and iOS, prompts participants three times a day with a request to rate their current mood, and an overview of the participant’s responses is shown in both the app and the web platform’s mood graph. The course consists of three lessons that were adapted from the Moodbuster for Depression intervention to fit the low-mood context of this study: (1) Introduction, (2) Psychoeducation, and (3) Pleasant activities. The first lesson has also been extended with some exercises based on motivational interviewing [29] to increase participants’ motivation for completing the course. For the purpose of the current study, an optional virtual coach has been embedded into the platform to provide automated support at the beginning and the end of every lesson and halfway through lesson 3, the longest lesson. For this study, participants are advised, but not obliged, to complete the intervention in a time span of 4 weeks. On completion, participants retain their access to the platform for about another 5 months. An overview of the intervention is shown in Table 2.

**Table 2 Tab2:** Overview of the Moodbuster Lite course as used in this pilot RCT

	Lesson 1	Lesson 2	Lesson 3
**Topic**	Introduction	Psychoeducation	Pleasant activities
**Time frame**	Week 1	Week 1	Weeks 2–4
**Length**	22 pages	11 pages	17 pages
**Conversations with virtual coach**	2	1–2	2–3

#### Automated support

##### Technical implementation

Automated support is delivered by a virtual coach in the form of an ECA. The ECA has been implemented in TyranoBuilder [30], a JavaScript-based software package for the development of visual novels that can be used to implement text-based dialogues with a virtual character. Our choice for TyranoBuilder was strongly motivated by the fact that applications can be exported in a browser format that allows them to be embedded in web pages (Fig. 2).

**Fig. 2 Fig2:**
[figure not shown]
The virtual coach embedded in the Moodbuster Lite platform

##### Embodiment

We have embodied the ECA using a single two-dimensional static cartoon-like character, taking into account the following recommendations from the literature on ECAs for motivational and coaching purposes. We have opted for a cartoon-like embodiment, as increased realism is not that important for involvement, distance, and use intentions, and may even set high expectations that the ECA cannot meet [31]. With regard to gender, we have chosen a female embodiment, as that is what people on average prefer [32]. The ECA is endowed with a number of facial expressions (friendly, smiling, compassionate, questioning; see Additional file 1), such that it can convey a sense of empathy [33]; we have not given the ECA negative facial expressions [34]. Finally, the ECA is designed to look as if it could be part of a therapy team, increasing its credibility by giving it a semi-formal friendly appearance and placing it before a background reminiscent of a therapy office [35].

##### Conversations

The conversations have been designed in collaboration with a licensed therapist and are based on guidelines for e-coaching [35] and principles of motivational interviewing [29]. Some examples of guidelines for providing feedback we have applied are to (1) use correct greetings and closings; (2) use communication skills such as beginning a message with a compliment; (3) structure feedback, for example by not giving feedback on more than two subjects; (4) refer to things the participants have done, such as completing exercises or recording their moods; and (5) keep text readable by using short, clear sentences. With regard to the motivational interviewing, we have focused on increasing an individual’s willingness to change behavior, as well as on their confidence in their ability to do so, both of which are important for being “ready” to change. Baseline values of a participant’s willingness to change and confidence in their ability to do so are established using the *importance and confidence ruler* exercises in lesson 1 of the intervention. If importance or confidence is low, the virtual coach presents specific exercises aimed either at increasing the discrepancy between a participant’s goals and their current behavior and emphasizing the importance of change, or at enhancing a participant’s self-efficacy and emphasizing confidence in their ability to change. These elements have been incorporated into all the conversations except the introductory and final ones, thus providing us with the general conversation structure shown in Table 3. Conversations after each lesson always take place, focused on providing feedback, while conversations before a lesson take place only if motivation is considered low or if the previous lesson received a negative evaluation. Such evaluations can be given by free text input at the end of each lesson, and a sentiment analysis algorithm [36] is used to determine its valence (negative or positive).

**Table 3 Tab3:** The differential stages in the conversations

Stage	Before the lesson	After the lesson
1	Greeting	Greeting
2	Compliment or positive note	Compliment or positive note
3	Reflection on evaluation of previous lesson	Reflection on current lesson
4	Re-evaluation of confidence or willingness	Confidence or importance work
5	Reference to current lesson	Reference to next lesson
6	Goodbye	Goodbye

##### Conversation trees

The conversations take place through text-based messages appearing beneath the virtual coach (see Fig. 2), and the user can proceed through the conversations by clicking the mouse button, or now and then by selecting or providing an answer when asked a question. Although much progress is currently being made in speech and natural language processing, we decided to represent our dialogues in textual conversation trees for several reasons: (1) speech and natural language processing are still far from flawless; (2) automatic interpretation and accurate response to semantic content are difficult; (3) conversation trees can be more easily interpreted by domain experts such as clinical psychologists; (4) conversation trees are deterministic, meaning that there is an exhaustive set of possible conversations that can be checked for inconsistencies; and (5) certain paths through the tree can be made conditional, for example based on an answer to an earlier question in the lesson or conversation, thus enabling conversations to be personalized. For illustrative purposes, Fig. 3 shows an excerpt from one of the conversation trees. The diamond represents a decision point in the conversation tree, rectangles represent utterances by the virtual coach, and circles indicate the corresponding facial expressions. The excerpt compares the latest confidence and willingness ratings provided by the user. If both values are higher than 6, the confidence and importance work is skipped. If one value is 6 or lower, the user is asked to re-evaluate the lower rating, prioritizing willingness over confidence, after which the tree continues with a suitable exercise. Additional file 2 provides additional information about the variables used in this excerpt.

**Fig. 3 Fig3:**
[figure not shown]
A conversation tree snippet from the dialogue that takes place after the second lesson

### Trial organization

The study is run from VU University Amsterdam, with no other study centers participating. The principal investigator is responsible for coordinating the study, which includes the recruitment of participants and the informed consent procedure, responding to questions and requests from (potential) participants, providing participants with access to the study materials, monitoring participants throughout the study, handling participant reimbursements, data collection, and reporting on the progress of the study to the steering committee members and medical ethical committee. The steering committee (see title page for members) agreed on the final version of this protocol and is responsible for reviewing the progress of the study, and for agreeing on changes to the protocol or study materials, if necessary, to keep the study running properly. Meetings of the steering committee are scheduled when necessary. The trial management committee is composed of the principal investigator and project leader. It is responsible for the study planning, organization of steering committee meetings, reporting to the medical ethical committee of study progress, maintenance of the trial master file, budget administration, and data verification. The trial management committee meets on a monthly basis. An IT team is responsible for the maintenance of the intervention platform and data collection from the platform. As this is a relatively small pilot study, there is no Stakeholder and Public Involvement Group.

Earlier large-scale research using the Moodbuster platform did not result in any known serious adverse events (SAEs) or serious adverse device events (SADEs). If SAEs or SADEs do occur, they will be discussed in the research team and reported to the Dutch Health and Youth Care Inspectorate. Any other adverse events reported spontaneously by the participants or observed by the investigators will be recorded. Due to the low-risk nature of the study, there is no anticipated harm and compensation for trial participation. Participants can contact an independent researcher if they run into issues during the study, and a licensed psychiatrist can be consulted in case issues of a medical or mental health related nature arise.

Significant amendments to the study protocol will be communicated to the medical ethical committee that approved the study, and an update will be made to the study information in the Dutch Trial Registry. Results will be published in a peer-reviewed journal and reported to the medical ethical committee that approved the study.

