### Assessments

Assessments will be taken after enrollment (T−1), at baseline (T_0_), and at the end of study participation 4 weeks after baseline (T_1_). Questionnaires will be self-administered and completed online. Table 1 provides an overview of the measures employed at specific time points.

**Table 1 Tab1:** Measures administered at each assessment interval

Questionnaire	Aim	Enrollment (T−1)	Allocation (T_0_)	Post-study (T_1_)
Mental health				
PHQ-9	*Screener*	X		
HADS-D	*Mental health*		X	X
Feasibility				
SUS	*System usability*			X
CSQ-I	*User satisfaction*			X
Study completion	*Reasons for non-adherence*			X
Motivation				
SMFL	*Current use*		X	X
Continued use	*Continued use*			X
Coach acceptance				
WAI-SR*	*Relationship*			X
Acceptance*	*Acceptance*			X

*Applies to the intervention group only

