#### Acceptance of the coach

Acceptance of the virtual coach will be assessed in the intervention group after 4 weeks (T_1_) using a set of six 7-point Likert-scale items. This scale has been previously used to measure attitudes toward a virtual discharge nurse [13] and has been adjusted to our context of iCBT. An overview of the items is provided in Table 4. Participants are asked to elaborate on their answers to each of these questions in an open text format.

**Table 4 Tab4:** Self-report measures of attitudes toward the virtual coach

Measure	Question	Likert-scale extremes
Satisfaction	How satisfied were you with the virtual coach?	Not at all–Very satisfied
Usability	How easy was it talking to the virtual coach?	Easy–Difficult
Continue	How much would you like to continue working with the virtual coach if the course continued?	Not at all–Very much
Relationship	How would you characterize your relationship with the virtual coach?	Complete stranger–Close friend
Preference	Would you rather have followed the course with or without the virtual coach?	Definitely prefer no coach–Definitely prefer virtual coach
Adherence	How likely is it that you will follow the virtual coach’s advice?	Not at all likely–Very likely

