#### Data management

On the informed consent form, participants will be asked if they agree to the use of their data in future research on the same topic at VU University, and to their data being shared with regulatory authorities when required. This trial does not involve the collection of biological specimens for storage. All raw data will be stored on a secure local server at the VU University in Amsterdam, which is regularly backed up. Paper-based documents will be stored in a keycard-secured archive at the Department of Clinical, Neuro- and Developmental Psychology. All participants will be de-identified upon randomization by linking their participant number to a random study participant code. In the study, participants will be referred to exclusively by that participant code, and the document linking the two numbers will be destroyed once the study is over and results have been disseminated. Because this study is relatively small and investigator-initiated, no data monitoring committee or auditing process is required. Because we do not expect serious negative outcomes for the participants, we do not conduct an interim analysis and there are no subsequent formal stopping rules.

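### Non-serious adverse events are collected only passively in an online trial whose T1 instruments ask nothing about unwanted effects, so a low count could not be read as evidence of safety

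*Protocol article*

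**What the plan says.** Under Trial organization, serious adverse events and serious adverse device events are to be discussed in the research team and reported to the inspectorate. For the rest the rule is: "Any other adverse events reported spontaneously by the participants or observed by the investigators will be recorded". The same section gives the principal investigator the task of "monitoring participants throughout the study", without a method or frequency, and adds: "Participants can contact an independent researcher if they run into issues during the study". Randomization and blinding states that the principal investigator knows the allocation.

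Under Assessments: "Questionnaires will be self-administered and completed online". Table 1 lists a depression screener, HADS-D, usability, satisfaction, reasons for non-adherence, motivation, and two coach measures. The coach measures carry the footnote "Applies to the intervention group only". One of them, described under Acceptance of the coach, has six items, and "Participants are asked to elaborate on their answers to each of these questions in an open text format".

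Both arms complete HADS-D at T0 and T1 and are prompted for mood three times a day. In both arms, participants who report not completing are asked why at T1.

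**The concern.** The collection method is stated, and it is passive, so this is not a detail left to a fuller document. Spontaneous reporting depends on the participant thinking an event worth mentioning and taking the initiative to do so. Investigator observation depends on contact. In a web and app course with software support or none, and with self-completed questionnaires, the document describes little from which an investigator would observe an event. Whatever the principal investigator does observe is seen with knowledge of the arm.

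The reassurance offered, that earlier research on the platform produced no known serious events, covers serious events only. It also predates the component under test, because the coach was embedded for this study. Non-serious unwanted effects of the coach are therefore both unknown and subject to the weakest collection rule. The pilot is meant to inform a larger trial. If it recorded few events, nobody could tell whether few occurred or few were reported.

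**Working it through.** **What each source can pick up**

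| Source | Arms | Asks about unwanted effects? |
|---|---|---|
| Spontaneous report or observation | both | no, passive |
| HADS-D at T0 and T1 | both | depressive symptoms only |
| Mood prompts, 3 × 28 = 84 | both | mood only |
| Reason for non-completion, T1 | both, non-completers only | not directly |
| Open text on six acceptance items, T1 | coach only | no; attitudes to the coach |
| Free-text lesson evaluation (Conversations) | availability to controls not stated | no; evaluates the lesson |

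No row solicits unwanted effects other than low mood, and the document does not say that any free-text field is screened for adverse events.

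**Size of a possible under-count**

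The protocol gives no adverse event rate, so there is no figure of its own to reproduce. The only input from the document is n = 35 per arm (Study design). The true risk p and the proportion captured c are assumptions.

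Expected recorded cases = 35·p·c. Chance of recording none = (1 − p·c)^35.

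| p | c | Expected | Chance of none |
|---|---|---|---|
| 10% | 100% | 3.5 | 0.90^35 = 2.5% |
| 10% | 60% | 2.1 | 0.94^35 = 11.5% |
| 10% | 50% | 1.75 | 0.95^35 = 17% |
| 10% | 30% | 1.05 | 0.97^35 = 34% |
| 10% | 20% | 0.7 | 0.98^35 = 49% |
| 5% | 100% | 1.75 | 0.95^35 = 17% |
| 5% | 30% | 0.53 | 0.985^35 = 59% |

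**What a zero count would exclude**

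With full capture, none in 35 has a one-sided 95% upper limit of 1 − 0.05^(1/35) = 8.2%, and none in 70 has 1 − 0.05^(1/70) = 4.2%. These limits reflect sample size alone. With capture c they apply to recorded risk, so the limit for true risk is divided by c: for one arm, 8.2%/0.6 = 13.7% or 8.2%/0.3 = 27.3%. Because c is unknown, no limit for true risk can be stated.

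**Unequal capture, if it existed**

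With equal true risk, the apparent risk ratio is the ratio of capture proportions: 0.60/0.30 = 2.0, or 0.40/0.30 = 1.33. Nothing in the document fixes these proportions or shows that they differ.

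**The case against.** The strongest reply is that this is a proportionate choice. The trial is a four-week, low-risk course for 70 people. It excludes candidates scoring 15 or higher on the PHQ-9 or 1 or higher on item 9. Safety is not among its aims, and no between-arm analysis of adverse events is described. Worsening of mood, a central foreseeable harm, is measured systematically and in the same way in both arms. Participants can contact an independent researcher, and a psychiatrist can be consulted. All of this stands, and it limits the weight of the point. It does not supply a source for unwanted effects other than mood.

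A reader might go further and infer three things that the document does not support.

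- **That counts will not be comparable between arms.** The recording rule is the same in both arms. The coach-only items ask about satisfaction, ease, continuation, relationship, preference and following advice, and nothing says their text feeds adverse event recording. Non-completers in both arms have a free-text question of their own. That question could even pull the other way: if the coach improves adherence, fewer coach-arm participants would be asked it.
- **That there is no routine contact.** The document describes no scheduled contact, but it does assign monitoring to the principal investigator.
- **That the protocol admits to neglecting harms.** The clause "Because we do not expect serious negative outcomes for the participants" (Data management) justifies having no interim analysis or stopping rules. It says nothing about how events are collected.

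**Conclusion.** The point holds as a limited weakness of design. Non-serious events enter the record only if volunteered or observed, the principal investigator is unblinded, and no T1 instrument asks about unwanted effects. Effects other than worsening mood may therefore be under-recorded, and a low count would not show that the course or the coach is safe. It would be too strong to say that events will be under-counted, since the document does not determine the capture rate.

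The figures are illustrations. At an assumed 10% risk, the chance that an arm of 35 shows no events rises from 2.5% with full capture to 17% or 49% with 50% or 20% capture. Unequal capture between arms is possible but not shown. No planned analysis is affected. The case for acting is that the change is nearly free, the pilot exists to prepare a larger trial, and the information is hard to recover once T1 has passed.

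**What to change.** Add one identical item to the online T1 assessment in both arms: whether the participant experienced any unwanted effect or new health problem since baseline, with a text field and the perceived relation to the course. Report these solicited events by arm, descriptively and separately from spontaneous or observed events. Leave events found only in the coach-acceptance text out of any between-arm description. State that a low spontaneous count will not be interpreted as evidence of safety.

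The cost is one extra question, one extra table, a slightly longer T1 and a higher, less flattering adverse event count. No visits or staff are needed. The item relies on four weeks' recall and reaches only those who complete T1. The 30 euro payment for completing T1, whatever the use of the course, gives non-adherers a reason to answer.

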### Primary outcome measures

#### Adherence

The primary outcome measure will be intervention adherence. According to the definition we have adopted, “adherence” describes the extent to which individuals are exposed to the content of the intervention [37]. Previously, this has been operationalized by dividing the number of completed sessions or modules by the maximum number [38], but because our 3-lesson course is relatively short, we will use the completed and maximum numbers of pages that make up the lessons. Including conversations with the coach, lesson 1 has 22 pages (20 in the control condition), lesson 2 has 13 (11 in the control condition), and lesson 3 has 20 pages (17 in the control condition). As a secondary way of measuring adherence, we will look at the *ecological momentary assessment* of mood via the smartphone application, whereby (similarly to adherence to the intervention content) we will operationalize adherence as the number of mood assessments made divided by the maximum possible number. There will be three mood assessments every day, meaning that participants can answer a maximum of 84 mood rating requests during the 4 weeks of the study.

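### The primary adherence score counts coach conversations in one arm only, so the two arms are not scored on the same content

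*Protocol article*

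**What the plan says.** The Adherence section of the protocol article takes adherence to be a matter of exposure: it "describes the extent to which individuals are exposed to the content of the intervention". Because the course has only three lessons, the score is built from pages: "we will use the completed and maximum numbers of pages that make up the lessons". The maxima are then given by arm: "Including conversations with the coach, lesson 1 has 22 pages (20 in the control condition), lesson 2 has 13 (11 in the control condition"). The third lesson counts 20 pages with the coach and 17 without.

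Two other places bear on the intervention-arm maximum. The Moodbuster Lite section says the coach gives "automated support at the beginning and the end of every lesson and halfway through lesson 3". Its Table 2 lists 2 conversations for lesson 1, 1–2 for lesson 2 and 2–3 for lesson 3. The Conversations section explains the ranges: conversations after a lesson always occur, but "conversations before a lesson take place only if motivation is considered low or if the previous lesson received a negative evaluation".

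Under Primary analysis, the completion score is compared between arms with a general linear model at the 0.05 level, and the result is to be used for the sample size of a larger trial.

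**The concern.** The Background frames the trial as the same course with and without the coach, and the question is whether the coach makes people get further through that course. The outcome should therefore give the same value to two people who have covered the same course material, whichever arm they are in. A score whose numerator and denominator contain coach pages in one arm only does not do this. It also mixes two quantities in the intervention arm: progress through the course, and exposure to the thing that was randomised.

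The conditional conversations add a second difficulty. Some intervention participants are never offered two of the conversations counted in their maximum, and the article does not say how these are scored. At stake is a small arm-dependent offset in the main estimate of a pilot whose stated purpose includes supplying that estimate to the next trial. A larger sample would not remove it.

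**Working it through.** **Inputs.** Pages per lesson, from the Adherence section: intervention 22, 13, 20; control 20, 11, 17. Conversations per lesson, from Table 2: 2, 1–2, 2–3. Number per arm, from Study design: 35. The documents give no SD for the score; 20 to 40 percentage points is assumed.

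**Reproducing the stated page counts.** Control pages plus the maximum number of conversations, at one page each: 20+2 = 22, 11+2 = 13, 17+3 = 20. All three match, so the intervention total is 55 against 20+11+17 = 48, a difference of 7. With the minimum number of conversations the counts would be 22, 12 and 19, total 53. The stated maximum thus includes the two conditional conversations, those before lessons 2 and 3.

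**Score for equal course content at lesson ends** (closing conversation included), under three ways of handling an untriggered conversation:

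| Course content finished | Control | Uncredited, maximum 55 | Credited (or shown), maximum 55 | Maximum = pages offered (53) |
|---|---|---|---|---|
| Lesson 1 | 20/48 = 41.7% | 22/55 = 40.0% (−1.7) | 22/55 = 40.0% (−1.7) | 22/53 = 41.5% (−0.2) |
| Lessons 1–2 | 31/48 = 64.6% | 34/55 = 61.8% (−2.8) | 35/55 = 63.6% (−0.9) | 34/53 = 64.2% (−0.4) |
| Whole course | 48/48 = 100% | 53/55 = 96.4% (−3.6) | 55/55 = 100% (0) | 53/53 = 100% (0) |

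**Direction elsewhere in the course.** Assume the pages run in the described order, with a coach page opening lesson 1. After k course pages of lesson 1 the intervention score is (k+1)/55 and the control score k/48.

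- k = 1: 2/55 = 3.6% against 1/48 = 2.1%, +1.6 points before rounding.
- k = 6: 7/55 = 12.7% against 6/48 = 12.5%, +0.2.
- k = 7: 8/55 = 14.5% against 7/48 = 14.6%, just below zero.

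With a maximum of 55 and neither conditional conversation shown, the intervention score is lower at 42 of the 48 course-page positions and higher only at the first 6. With both shown, it is also slightly higher at a few later points, for example just after the conversation opening lesson 3: 36/55 = 65.5% against 64.6%, +0.9. An individual gap can reach −5.5 points, for someone who finishes all 48 course pages but not the closing conversation and was shown neither conditional one: 52/55 = 94.5%.

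**Size against sampling error.** SE of the arm difference = SD × √(2/35): 20 × 0.239 = 4.8 points and 40 × 0.239 = 9.6 points. The full 3.6-point completer gap is therefore about 0.8 to 0.4 SE. Its effect on the arm mean is diluted by the share who complete. If 50% to 80% complete and none triggers a conditional conversation (both assumed), completers contribute 0.5 × 3.6 = 1.8 to 0.8 × 3.6 = 2.9 points.

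**The case against.** The strongest reply is that the coach is part of the intervention in that arm, so dividing by each arm's own maximum is a recognisable normalisation and fits the exposure definition. That is fair as to the definition, but it does not answer the trial's question, which concerns the coach's effect on use of the shared course.

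The second reply concerns the 53/55 ceiling. The article says a conversation may not take place; it does not say that its page is absent or uncredited. Fixed lesson lengths beside ranges of conversations are compatible with a fixed page sequence, and the Moodbuster Lite section places the coach "at the beginning and the end of every lesson and halfway through lesson 3, the longest lesson" without any condition. The full protocol or analysis plan may settle how skipped conversations are scored. This stands: the ceiling is the literal reading of a maximum of 55 but rests on an unstated rule. Completers tie with control at 100% if they were shown every conversation, if skipped pages are credited, or if the maximum is the pages offered.

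Three stronger readings are tempting, and the documents do not support them.

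- A reader might infer that equal exposure always scores lower with the coach. It does not, as the early positions and the ties show.
- A reader might infer that a coach who succeeds in motivating people lowers the arm's score. The effect is confined to two pages out of 55, depends on the unstated rule, and could be far outweighed by people finishing more of the course.
- A reader might infer that the next trial would more than double in size. Total N = 2 × 2 × (1.96 + 0.84)² × SD²/d² gives about 284 at SD 30, a 10-point gain and 80% power, and about 700 if the gain appears as 6.4 points. But that applies the full completer gap to every participant, and the SD and the gain are both assumed.

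**Conclusion.** The defect holds in a limited form. The stated score uses maxima of 55 and 48 that include coach conversations in one arm only, so the arms are not measured on the same content, and exposure to the randomised component enters the outcome. That is so on every reading of how untriggered conversations are handled.

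The numerical consequence is small and not always in one direction. At lesson ends it runs from 0 to −3.6 points with a fixed maximum of 55, and shrinks to under half a point if the maximum is the pages actually offered. Very early stoppers gain up to about 1.6 points. Even the full 3.6 points is below one SE for assumed SDs of 20 to 40, so it is unlikely by itself to change the pilot's conclusion.

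It should still be corrected before analysis, because the offset is systematic, it enters the estimate that is to size the next trial, and it is easy to remove. Confidence is high that the arms are scored differently and only moderate for the 96.4% ceiling.

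**What to change.** Define the primary outcome identically in both arms: the number of course pages common to both arms that were completed, divided by the common total. Leave coach pages out of both numerator and denominator. A full completer then scores 48/48 = 100% in either arm, and equal course exposure gives a difference of zero. Report coach conversations completed out of those triggered separately, for the intervention arm only.

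The common total of 48 must first be reconciled with Table 2, whose lengths of 22, 11 and 17 (total 50) match the intervention count for lesson 1 but the control counts for lessons 2 and 3. Using the pages actually offered as the denominator would be a weaker repair: it removes the ceiling but still counts coach pages in one arm only.

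The cost is one sentence in the outcome definition and a filter on the log-file extraction. It assumes that coach pages can be identified in the page logs, which the article does not confirm.
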